### Adverse outcomes

Any adverse outcomes involving trial participants such as surgical site infection, metal wear infection, excessive bleeding, change in vision, death or common perioperative complications such as deep vein thrombosis, pulmonary embolism or pulmonary infections will be documented and treated accordingly. If warranted, patients will be referred to other medical specialist teams. Any post-trial care and compensation required will be as per Queensland Health standard arrangements.

### Power calculation

An estimated 200 patients will be required for a sample size that will produce significant results. This is based on two-sided testing with a power calculation of 80% and is established from local department outcome estimates and results from studies by Van Hout et al., Hurrell et al. and Van Den Bergh et al. [10, 15, 16]. The variable that required the largest projected sample size to obtain a statistically significant result was the adequacy of post-operative fracture reduction as demonstrated radiographically. The power calculation was performed by [name], a biostatistician from the University of Queensland (UQ) School of Population Health.

Due to the low level of evidence available in the current literature, the sample size calculations may not be reliable and estimates were not possible for all variables being proposed in this study. Subsequently, a mid-study analysis will be conducted to more accurately assess the predicted sample size calculations. It is estimated that from the average number patients presenting yearly with ZMC and ZA fractures at the RBWH, this study will take approximately 2 years to complete. If the mid-study analysis identifies a statistically significant result, the study will potentially be terminated early. The decision to terminate the trial or continue after the mid-study analysis will be at the discretion of the study authors.

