### Randomisation

The patients who are recruited to the trial will be randomised into two groups, intraoperative computed tomography scan (intervention) and no intraoperative computed tomography scan (control). The patient will be randomised by the oral and maxillofacial surgery department nurse, who will blindly select a table tennis ball from a container. The container will hold only two balls, with one ball having the word “intervention” and the other ball having the word “control” written on them. Whichever ball is selected by the nurse, is the group to which the patient is allocated.

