### Evaluation of outcomes

The two-sample *t* test will be used for analysis of continuous variables. The chi-square test will be used for analysis of categorical variables and for all data, a *p* value <0.05 will be considered significant. The software program SPSS will be used for all statistical analysis. Subgroup analysis based on the severity of the fractures will also be conducted. Patients will be analysed as per their treatment but non adherence will be considered in the final presentation of data. An interim analysis will be also be undertaken. There are no other audits of trial conduct planned.

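### Sample-size re-assessment is tied to a comparative mid-study look with p<0.05 kept for all data; if the new size follows the observed difference, the false-positive rate can rise to about 0.060–0.075 and the new size is close to uninformative

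*Protocol article*

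**What the plan says.** Power calculation states that "An estimated 200 patients will be required for a sample size that will produce significant results", for two-sided testing at 80% power. The variable that drove this number "was the adequacy of post-operative fracture reduction as demonstrated radiographically". The calculation "is established from local department outcome estimates and results from studies by" three cited sources; the article gives no rates and no target difference. It then concedes that the calculation may be unreliable and that some variables could not be estimated at all, and for that reason "a mid-study analysis will be conducted to more accurately assess the predicted sample size calculations".

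The same paragraph allows the trial to end early if this analysis is significant, and adds: "The decision to terminate the trial or continue after the mid-study analysis will be at the discretion of the study authors".

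Evaluation of outcomes mentions an interim analysis, names the two-sample t test and the chi-square test, and says that for all data a p "value <0.05 will be considered significant". Neither section gives a basis for re-sizing, a minimum, a maximum, or a different level for the interim or final test.

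**The concern.** One analysis has two jobs. Testing for significance requires splitting the data by arm, so whoever revisits the sample size can see the observed difference. The obvious way to revisit a power calculation whose inputs are distrusted is to re-run it with the interim arm results.

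Two things follow if that is done. First, the amount of further data depends on how the comparison looks at the interim. An ordinary chi-square or t test on the pooled data ignores that dependence and need not hold 5%, even if the trial is never stopped early. Second, the difference seen in half the patients is too noisy to size a trial. A lucky interim would call for almost no further patients and an unlucky one for an unattainable number, even when the original assumption was correct.

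This is distinct from the unadjusted efficacy stop. A stopping boundary alone would not remove it, and its remedy is different.

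**Working it through.** **Inputs from the article:** total 200, two-sided 0.05, 80% power, two arms with equal allocation in expectation.

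**Assumptions:** mid-study means 100 of 200 patients (50 per arm); the outcome is treated as binary; all rates, floors and caps are mine.

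**1. The stated 200.** It cannot be checked directly, because no rates are given. It is consistent with, for example, 75% vs 90% adequate reduction, mean 82.5%, without continuity correction:

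n per arm = [1.960·√(2·0.825·0.175) + 0.842·√(0.75·0.25 + 0.90·0.10)]² / 0.15² ≈ 99.5, so 100 per arm and 200 in total.

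70% vs 86.3% and 80% vs 93.4% also give 100 per arm.

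**2. Re-sizing from the observed difference.** With interim statistic z1 on 100 patients, the total giving 80% power at the observed effect is

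N = 100·[(1.960 + 0.842)/|z1|]² ≈ 785/z1².

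The final statistic is Z = [10·z1 + √(N−100)·z2]/√N, rejected if |Z| > 1.960. Under the null, z1 and z2 are independent standard normal. The error is the conditional rejection probability averaged over z1. With N fixed at 200 this returns 0.0500, as it should. With no early stop:

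| Rule for total N | Two-sided error |
|---|---|
| Increase only, 200–300 | 0.056 |
| Increase only, 200–400 | 0.060 |
| Increase only, 200–600 | 0.064 |
| Increase only, 200–800 | 0.066 |
| May also fall, 100–400 | 0.068 |
| May also fall, 100–600 | 0.072 |
| May also fall, 100–800 | 0.074 |
| Keep 200 if the need exceeds the cap (300–800), increase only | 0.048–0.049 |
| The same, decrease allowed | 0.056–0.057 |

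Binary simulation (400,000 null trials per setting) agrees: for 200–400 it gives 0.060 at a 75% rate and 0.061 at 85%, against 0.049–0.051 for the fixed design.

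**3. Precision of the new N when the design effect is true.** Then z1 ~ N(2.802·√0.5, 1) = N(1.981, 1).

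- Median: |z1| = 1.981, N = 785/3.924 ≈ 200.
- 10th percentile of N: |z1| = 3.26, N ≈ 74.
- 90th percentile of N: |z1| = 0.72, N ≈ 1,500.
- Interquartile range: about 111 to 458.
- About 20% of results fall between 150 and 250, 21% are at or below the 100 already enrolled, and 28% exceed 400.

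The Background gives about 160 of these patients per year at the hospital, so 1,500 would take 1,500/160 ≈ 9.4 years even if every one were eligible and consented.

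**4. Pooled-rate alternative.** Re-sizing from the combined rate, with an assumed difference of 0.15 held fixed, gives a simulated error of 0.050–0.051. For 75% vs 90% the new N has an interquartile range of about 176 to 221.

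**5. Interaction with stopping.** Two looks, each at 0.05 and correlated √0.5, give 0.083. Adding increase-only re-sizing to 400 gives 0.093, and to 600 gives 0.097.

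**The case against.** The strongest objection is that the article never says the new total is calculated from the arm difference. It says only that the calculation will be assessed more accurately, and one look can supply both a pooled rate and a significance test. This stands: a reader might infer that the plan prescribes re-sizing on the comparative result, and the text does not support that. It leaves the route open, which is all that is claimed here.

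A reader might also infer that the final p-value is bound to be anti-conservative. It is not: pooled re-sizing and some effect-based rules stay near 5%. Nor does the authors' discretion extend to choosing a new N, since that sentence covers only terminating or continuing.

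The inputs are assumed, the grade has three levels rather than two, and the larger caps are unlikely given the recruitment period. That limits the size: with a cap of 400 and no decrease, the excess is about one percentage point.

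Finally, re-sizing detail is often left to a fuller document. That excuses missing formulas. It does not excuse what the article does state: one comparative look serving both purposes, and one unadjusted level for all data. The overlap with the stopping rule is real, and the unadjusted stop is the larger problem, but a boundary for it would leave this one in place.

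**Conclusion.** The concern holds in conditional form. The plan puts sample-size re-assessment inside a comparative analysis, keeps p<0.05 throughout, and does not exclude re-sizing on the observed difference. If that is done, the error can reach about 0.060 to 0.075 without any early stop under clipped rules with caps of 400 to 800; a cap of 300 gives 0.056, and keep-200 rules give 0.048 to 0.057. The more practical consequence is the instability of the new N, about 74 to 1,500 at the 10th and 90th percentiles even when the design effect is right. A step meant to repair an unreliable calculation would then yield a less reliable one. These figures assume a look at 100 of 200 patients and a binary outcome. The inflation is modest, so this is a change that should be made rather than a fatal flaw.

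**What to change.** In Power calculation, state that re-estimation uses only the distribution of the radiographic reduction grade with both arms combined, prepared without allocation labels. The difference used in the original power calculation should be stated and held fixed. Set a floor of 200 and a maximum in advance.

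If the observed difference is to be used instead, fix the stage weights in advance and combine the two stages with an inverse-normal combination test.

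Pooled re-sizing adds practically no inflation of its own, but it does not by itself justify a final level of 0.05. That level may stay only if the efficacy stop at this look is removed or given its own pre-set boundary, with the final critical value to match.

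The cost is one paragraph and no extra patients in itself. The small downside is that N can no longer respond to the observed effect. If the mid-study analysis has already taken place (recruitment began in August 2016), the trial report should state which basis was used.

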## Methods

### Study objectives

The primary objective of the trial is to determine if intraoperative CT imaging improves clinical outcomes for zygomaticomaxillary complex and zygomatic arch fractures that are managed surgically. This will be assessed through the following variables:
Post-operative radiographic reduction adequacyNeed for revision surgeryNumber of intra-operative re-reductionsPost-operative diplopiaFacial profile restorationSurgical incision and scarring

The secondary objective of the trial is to ascertain whether intraoperative CT imaging has a significant impact on the length of surgery and whether it affects the outcomes of delayed versus early surgical treatment outcomes [15].

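### The protocol lets the authors stop mid-study on any result with p<0.05, naming neither an outcome nor a boundary, which raises type I error above the nominal level

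*Protocol article*

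**What the plan says.** All places are in the protocol article.

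- **Evaluation of outcomes** sets one criterion for all data: a p "value <0.05 will be considered significant". The same section adds: "An interim analysis will be also be undertaken". No separate interim or final threshold is given.
- **Power calculation** first gives the look a planning purpose: "a mid-study analysis will be conducted to more accurately assess the predicted sample size calculations". It then adds a stopping rule: "If the mid-study analysis identifies a statistically significant result, the study will potentially be terminated early". On who decides, it says: "The decision to terminate the trial or continue after the mid-study analysis will be at the discretion of the study authors".
- **Power calculation** identifies radiographic reduction adequacy as the variable needing the largest sample. It does not make it the outcome on which the trial may stop.
- **Study objectives** lists six variables under the primary objective: radiographic reduction adequacy, revision surgery, intra-operative re-reductions, diplopia, facial profile, and incision and scarring. Length of surgery is a secondary objective.

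**The concern.** Read together, these sections describe a test at 0.05 mid-study, a possible stop on any hit, and otherwise a second test at 0.05. Two chances to cross the same line give a higher false-positive rate than one. A trial stopped on a chance high also tends to overstate the effect.

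Leaving the outcome open adds two problems. Each further variable that may trigger the stop adds chances of a false alarm. Some variables can also differ between arms for reasons that say nothing about patient benefit. The article presents this trial as the first randomised evidence on the question, so an early stop on a chance or built-in difference would be costly.

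**Working it through.** **The plan's own figure.** The total of 200 (two-sided, 80% power) cannot be reproduced, because no outcome rates are given. At 100 per arm, 80% power corresponds, for example, to good-reduction rates of 70% against 86%, or 80% against 93%. The figure is neither confirmed nor refuted, and this point does not depend on it.

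**Inputs.** Per-test threshold 0.05 (Evaluation of outcomes), two-sided testing (Power calculation), one interim look, six variables (Study objectives). *Assumption:* the look is at information fraction t = 0.5, inferred only from the term mid-study; 0.25 to 0.75 is also shown. Test statistics are taken as normal, so sparse outcomes such as revision surgery would differ somewhat.

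**1. One outcome, two looks.** With corr(Z1, Z2) = √t, the error is 1 − P(|Z1|<1.96 and |Z2|<1.96).

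| t | Overall two-sided error |
|---|---|
| 0.25 | 9.1% |
| 0.50 | 8.3% |
| 0.75 | 7.3% |

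**2. Discretion.** If a share q of significant interims leads to a stop and the rest continue to the final test, the error at t = 0.5 is 0.05 + q × (0.0831 − 0.05).

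- q = 0: 5.0%
- q = 0.5: 0.05 + 0.5 × 0.0331 = 6.7% (6.6% by simulation)
- q = 1: 8.3%

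**3. Six variables, all null, t = 0.5.** Under independence, one look gives 1 − 0.95^6 = 26.5% and two looks give 1 − (1 − 0.0831)^6 = 40.6%. The correlated cases were simulated with 500,000 runs and equal correlation ρ between outcomes. The protocol gives no correlations.

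| ρ | Final look only | Either look | Added by the look |
|---|---|---|---|
| 0 | 26.5% | 40.6% | 14.1 points |
| 0.3 | 24.2% | 37.2% | 13.0 points |
| 0.5 | 20.7% | 32.2% | 11.5 points |
| 0.7 | 16.4% | 25.8% | 9.4 points |
| 0.9 | 10.8% | 17.3% | 6.5 points |

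Most of the either-look figure is present with no interim at all. Only the last column belongs to the mid-study rule.

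**4. Triggers that are not null.** Under Study groups, only the intervention arm has a scan that can prompt a re-reduction, so a difference in that count is built in. Ethical considerations expects CT to add 10 minutes to surgery. With 50 per arm at the look, the chance of p<0.05 on length of surgery is about Φ(10 / (SD × √(2/50)) − 1.96). The SDs are assumptions.

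- SD 15 min: Φ(3.33 − 1.96) = 92%
- SD 20 min: Φ(2.50 − 1.96) = 71%
- SD 30 min: Φ(1.67 − 1.96) = 38%

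**5. Boundaries for one outcome at t = 0.5.**

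- O'Brien-Fleming, constant 1.977: interim |Z| > 1.977 × √2 = 2.796 (p<0.0052), final |Z| > 1.977 (p<0.048), overall 5.0%.
- Haybittle-Peto, interim p<0.001 and final 0.05: overall 5.02%.
- The fixed O'Brien-Fleming pair used at t = 1/3 instead gives 5.1%, so it needs recomputing if the final N changes.

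**The case against.** **An analysis plan not shown may hold a boundary.** It may. But the protocol does not merely leave the matter open. It applies 0.05 to all data and leaves stopping to the authors, so a boundary elsewhere would conflict with this text and the two would need reconciling.

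**Stopping is only potential.** This stands. The 8.3% is an upper figure for a look at half information, and the rate falls towards 5% as fewer significant interims are acted on.

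**A reader might conclude that the mid-study rule produces a 32-41% false-positive rate.** The documents do not support that. Six unadjusted tests carry 21-27% with no interim, the range assumes correlations of 0-0.5 that the protocol does not give, and re-reductions are not a plausible null. With five variables under independence the figures are 1 − 0.95^5 = 22.6% for one look and 1 − (1 − 0.0831)^5 = 35.2% for two.

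**A reader might also infer that sample size is re-estimated from arm-level results, inflating error further.** The article does not say whether pooled or arm-level data are used. Nor does it claim an overall 5% error rate; 0.05 is a per-test threshold.

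**Conclusion.** The point holds as a defect in what the protocol states: an unadjusted, discretionary efficacy look with no named outcome. For a single outcome, the two-sided type I error lies between 5% and about 8.3% with a look at half information. The upper figure is 7.3-9.1% for a look at 75% down to 25%, and is reached only if every significant interim is acted on. With six possible triggers, the look adds roughly 11-14 percentage points to an existing 21-27%. That part is illustrative: it assumes all nulls true and correlations of 0-0.5, and the addition is smaller at higher correlation. Separately, the trigger could be met by re-reductions or length of surgery. A difference there would be real, not a false positive, but it would not show that patients benefit.

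**What to change.** 1. Name radiographic reduction adequacy as the only outcome that can stop the trial early.
2. Set a boundary. Either use Haybittle-Peto (interim p<0.001, final 0.05), or an O'Brien-Fleming-type boundary through a spending function. The latter is p<0.0052 and p<0.048 if the look is at half of the final N, recomputed if N changes.
3. State that the sample-size reassessment uses pooled, blinded grade frequencies.
4. Alternatively, delete early stopping and keep only the blinded reassessment.
5. Trial status puts the start of recruitment in August 2016 and its expected end in September 2019, so the look may already have happened. If so, report what was tested and decided, and account for it in the final threshold.

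**Cost.** If the look is still to come, this is a short amendment. An early stop becomes less likely and, with O'Brien-Fleming, the final alpha falls slightly from 0.05 to 0.048. If the look has taken place, an amendment alone cannot repair it.

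**Limit.** This does not address multiplicity across the six variables at the final analysis. With the other five still tested at 0.05, the chance of at least one false positive stays at about 21-27% under the same assumptions.

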### Study design

This is a prospective, single-centre, double-blinded, RCT. It will be conducted by the Oral and Maxillofacial Surgery department (OMFS) at the Royal Brisbane and Women’s Hospital in Brisbane (RBWH), Australia. This is a tertiary teaching hospital and major trauma centre for the city of Brisbane and the state of Queensland. The study was approved by the Royal Brisbane and Women’s Hospital Human Research Ethics Committee (reference number HREC/16/QRBW/18) on 27 July 2016 prior to recruitment of patients. This study complies with the National Health and Medical Research Council’s (NHMRC) National Statement on Ethical Conduct in Human Research (2007). The trial was registered with the Australian and New Zealand Clinical Trials Registry (registration number ACTRN12616000693426) on 26 May 2016 prior to patient recruitment. Please see the Standard protocol items: recommendation for interventional trials (SPIRIT) figure (Fig. 1) for an illustration of the timeline for enrolment, interventions and assessments in the trial. The SPIRIT checklist has been completed for further information (Additional file 1).

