### Recruitment and consent

All patients who present to the OMFS of the RBWH, with an isolated ZMC fracture or an isolated ZA fracture, will be screened for a position on the trial. As RBWH is an adult hospital, all patients will be 16 years of age or older and they must require surgical management of their ZMC or ZA fracture to be included in the trial. Criteria for exclusion from the trial include the following:
PregnancyInability to give informed consentConcomitant non-zygomatic facial fractures (including orbital floor fractures) or bilateral zygomatic fracturesNot wishing to be part of the study

If a patient fulfils the criteria to participate in the trial, they will be informed verbally of what the trial involves, the risks associated with it and their role. They will also be given written information on the trial, the risks involved and all of their rights, including the ability to withdraw at any stage. If the patient is happy to participate, they will be given a consent form to complete. The aforementioned tasks of obtaining informed consent and recruiting patients to the trial will be completed by an oral and maxillofacial surgery registrar (training surgeon) or consultant (surgeon).

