### Blinding

The patients will not be informed of the group to which they are randomised. Concurrently, the clinician assessing the fracture reduction on the post-operative radiographs will be blinded to the arm of the trial to which the patient has been allocated. The surgeon operating on the patient will not be blinded as this is impossible, given they will be witness to whether or not intra-operative CT is performed. The physician assessing the patient in clinic at both 1 week and 6 weeks post-surgery will not be blinded to the patient’s study group. Blinding of this assessment would be extremely difficult as the physician assessing the patient will be involved with the operation and hence know the allocated group. The clinician assessing the post-operative radiographic reduction will not perform any of the operations in the trial.

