### Data collection, management and confidentiality

Data from the post-operative radiographic assessments will be entered directly into the trial Excel spreadsheet. All data recorded on the post-operative assessment forms (Figs. 2 and 3) will be transferred to the trial Excel spreadsheet. This Excel file will be stored on a single, password-protected personal computer. At the completion of the trial, the Excel spreadsheet will be transferred to a password-protected computer within the OMFS department at the RBWH. It will be stored on this computer for 15 years. All hard copies of the consent and post-operative assessment forms will be stored in a designated trial folder, which will be stored in a locked room in the OMFS department at the RBWH. At the completion of the trial, this folder will remain in the OMFS department for 15 years. The final trial data set will only be accessible to the authors of the trial.

Data on patients’ names, date of birth, gender, address and occupation will not be collected. Patients will only be identified by their unique record number (URN), otherwise known as a medical record or hospital record number. The URNs will be removed from the data pool prior to statistical analysis.

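### The choice to stop or continue after a between-arm mid-study look is left to the study authors, with no described separation from the department's unblinded clinical staff

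*Protocol article*

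**What the plan says.** Under Power calculation, the mid-study look has two purposes. One is resizing: "a mid-study analysis will be conducted to more accurately assess the predicted sample size calculations". The other is a possible early end: "If the mid-study analysis identifies a statistically significant result, the study will potentially be terminated early". The choice is then assigned: "The decision to terminate the trial or continue after the mid-study analysis will be at the discretion of the study authors".

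On who runs the trial, Study design says: "It will be conducted by the Oral and Maxillofacial Surgery department (OMFS) at the Royal Brisbane and Women’s Hospital in Brisbane (RBWH), Australia". Under Recruitment and consent, registrars or consultants of that specialty recruit and take consent. Under Blinding, the operating surgeon knows the allocation, and so does the clinic reviewer: "The physician assessing the patient in clinic at both 1 week and 6 weeks post-surgery will not be blinded". Under Follow up and outcomes, registrars or consultants grade diplopia, scarring and facial profile. The post-operative radiographs are graded by a different surgeon, who is blinded to group and takes no part in operations or clinical assessments.

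After mentioning the interim analysis, Evaluation of outcomes adds: "There are no other audits of trial conduct planned". It also says that patients are analysed by the treatment they received.

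**The concern.** A stopping decision that turns on a between-arm test, and is left open to discretion, will ordinarily be made with some knowledge of how the arms compare. In this trial most clinical roles already carry knowledge of the allocation. Keeping the interim trend from those staff is therefore one of the few protections left for the outcomes they influence, and the text provides none.

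If the trend becomes known and the trial goes on, several things can drift in its direction: subjective grades, the threshold for revision or for re-reducing a fracture, adherence to allocation, and which patients are approached. The final analysis pools both halves, so any drift enters the reported effect. Because patients are analysed by treatment received, crossover prompted by the trend would also change the groups being compared. A corrected significance level at the interim look deals with repeated testing. It does not remove a drift of this kind.

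**Working it through.** **Step 1: is the look comparative?** Yes. Early termination depends on a statistically significant result, and that requires a test between arms. A blinded sample-size review alone could not trigger it.

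**Step 2: who decides, and who is exposed?**

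| Role | Knows allocation? | Separated from the interim decision in the text? |
|---|---|---|
| Study authors (stop or continue) | Not stated | They make the decision |
| Recruiting registrar or consultant | Not before the draw, which a nurse makes | No separation described |
| Operating surgeon (re-reduction, repeat scan) | Yes | No separation described |
| Clinic reviewer (diplopia, scarring, facial profile) | Yes | No separation described |
| Radiographic assessor | No | Not needed for grading: cannot favour an arm without knowing it |

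Five of the six variables under Study objectives are open to influence by unblinded staff: diplopia, facial profile, scarring, need for revision and number of re-reductions. The sixth, radiographic reduction, set the sample size. Its grading is protected, although a surgeon's conduct in theatre could still affect the reduction itself.

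**Step 3: would the look be informative?** The plan gives 200 patients, 80% power and two-sided testing, with significance at 0.05. I assume the look falls at 100 patients, about 50 per arm. At full size the expected test statistic under the design effect is 1.96 + 0.84 = 2.80. At half the information it is 2.80/√2 = 1.98, so power at 0.05 is about 50%. A visible trend at mid-study is realistic if the effect is real. The article gives no event rates, so 200 cannot be reproduced from it; this point does not depend on that figure.

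**Step 4: illustration of size.** All rates and shifts here are assumptions. There is no true effect, the unfavourable grade has rate p0, and grading of the second 50 CT patients is shifted by s in favour of CT. The final test is a chi-square at 100 per arm.

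Worked by hand for p0 = 0.20 and s = 0.10:
- CT rate over both halves: (50×0.20 + 50×0.10)/100 = 0.15, so the spurious difference is 0.05.
- Standard error used by the test: √(2×0.175×0.825/100) = 0.0537.
- Actual standard error: √(0.20×0.80/100 + (50×0.20×0.80 + 50×0.10×0.90)/100²) = √0.00285 = 0.0534.
- P(significant for CT) = 1 − Φ((1.96×0.0537 − 0.05)/0.0534) = 1 − Φ(1.04) ≈ 0.150. The other tail adds about 0.002, for a total of about 15.2%.

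Simulation of 200,000 trials per cell gives 15.4% for this case, and overall:

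| p0 | s = 5 points | s = 10 points | s = 15 points |
|---|---|---|---|
| 0.20 | 7.5% | 15.4% | 30.2% |
| 0.30 | 6.8% | 12.4% | 22.2% |
| 0.40 | 6.5% | 11.2% | 19.2% |

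With no shift the rate is 5.1% to 5.2%.

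**Step 5: how far the illustration depends on its form.** The table always shifts toward CT, but with no true effect CT leads at mid-study in only about 45% to 46% of trials. If instead the CT rate moves by s in whichever direction the interim trend points (no move on a tie), the same inputs give about 11% to 46%. If the shift toward CT runs from the first patient, they give about 11% to 92%. The chosen shift and its pattern determine the answer.

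**The case against.** The strongest reply is that the harm rests on inference. The text shown does not say that the authors recruit, operate or review patients, nor who runs the mid-study analysis, nor in what form its result is reported. The authors could decide on a bare report of significance or non-significance, and a condensed article may leave such detail to the full protocol. This stands against saying that arm-level results go to the authors. It does not answer the point that the article itself fixes an open, discretionary decision on a comparative look.

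A reader might also take the data-access statement ("The final trial data set will only be accessible to the authors of the trial") as showing that the authors see interim results. It concerns the final data set only and does not support that.

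A reader might infer that the outcome behind the sample size is graded by people who know the trend and the arm. The documents say the opposite: that assessor is blinded and separate. The nurse's draw also limits selection by arm, though not a change in whom staff approach.

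Finally, unblinded clinical grading is a problem from the first patient and may be the larger one. That is correct, and separating the interim results would not remove it.

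**Conclusion.** The point holds in limited form. The protocol places a discretionary stop-or-continue decision, based on a between-arm test, with the study authors, and describes no separation from the unblinded staff of the department that runs the trial. It rests on one assumption: that some authors also recruit, operate or review patients, or would pass the trend to those who do. In a trial run by a single department this is likely, but it is not shown.

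The exposure covers the clinical grades, revision and re-reduction decisions, adherence to allocation and whom staff approach. It does not extend to the grading of radiographic reduction.

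The size cannot be derived from the documents. It would be tempting to quote 6.5% to 30% as the trial's false-positive rate. That is not supported: the figures are illustrative, for an assumed 5 to 15 point shift toward CT in one clinically graded outcome, and they ignore early stopping. The change is worth making because it is cheap and removes an avoidable source of bias, not because a given inflation has been demonstrated.

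**What to change.** Replace the discretion sentence under Power calculation with a rule written before the look. Have the biostatistician already engaged for the power calculation run the mid-study comparison and return to the authors only stop or continue, plus any revised total. State that no arm-level results go to anyone who recruits, operates, decides on revision or grades outcomes.

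Recruitment began in August 2016 and was expected to end in September 2019, so the look may already have happened. In that case, state who saw arm-level results, and report first-half and second-half effects side by side as a check.

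The cost is a short protocol amendment and some hours of an existing collaborator's time. The authors give up sight of interim results and their open discretion. Bias from unblinded clinical grading remains and has to be dealt with separately.
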